# Smoking Cessation Using Wearable Sensors: Protocol for a Microrandomized Trial

**DOI:** 10.2196/22877

**Published:** 2021-02-24

**Keywords:** mHealth, microrandomized trial, smoking cessation, mindfulness, tobacco, mobile phone

## Abstract

**Background:**

Cigarette smoking has numerous health consequences and is the leading cause of morbidity and mortality in the United States. Mindfulness has the ability to enhance resilience to stressors and can strengthen an individual’s ability to deal with discomfort, which may be particularly useful when managing withdrawal and craving to smoke.

**Objective:**

This study aims to evaluate feasibility results from an intervention that provides real-time, real-world mindfulness strategies to a sample of racially and ethnically diverse smokers making a quit attempt.

**Methods:**

This study uses a microrandomized trial design to deliver mindfulness-based strategies in real time to individuals attempting to quit smoking. Data will be collected via wearable sensors, a study smartphone, and questionnaires filled out during the in-person study visits.

**Results:**

Recruitment is complete, and data management is ongoing.

**Conclusions:**

The data collected during this feasibility trial will provide preliminary findings about whether mindfulness strategies delivered in real time are a useful quit smoking aid that warrants additional investigation.

**Trial Registration:**

Clinicaltrials.gov NCT03404596; https://clinicaltrials.gov/ct2/show/NCT03404596

**International Registered Report Identifier (IRRID):**

DERR1-10.2196/22877

## Introduction

### Tobacco Use and Stress

Cigarette smoking has numerous adverse health consequences and is the leading cause of morbidity and mortality in the United States [1]. Determining how to prevent relapse following a quit attempt is key to successful long-term tobacco abstinence. When considering predictors of relapse, the experience of stress, or negative affect, is strongly associated with the risk of relapse [2,3], and high stress is related to an increased likelihood of lapse during a smoking quit attempt [4]. Developing smoking cessation interventions that target stress are needed and may be particularly useful for individuals with low socioeconomic status (SES), given increased exposure to chronic stressors and other negative life events (eg, discrimination and violence) [5-8].

### Mindfulness as a Quit Smoking Aid

One potential skill that could aid individuals in successful cessation, by enhancing resiliency to stressors, is the cultivation of mindfulness. Mindfulness is a multifaceted construct and is often described as the ability to pay attention to the present moment, with purpose and without judgment [9]. When applied to making a behavior change, such as quitting smoking, mindfulness is hypothesized to decrease automaticity, such that an individual chooses how to respond in a given situation (vs automatically reaching for a cigarette, for instance) [10-13]. Mindfulness is also posited to enhance an individual’s ability to be present with discomfort, which is particularly relevant when managing cravings and symptoms of withdrawal [14]. Mindfulness may be particularly useful for those experiencing high levels of stress, as it teaches skills that are applicable to a host of experiences (eg, managing physical and emotional distress) and is not specific to only changing the targeted behavior of smoking.

Mindfulness-based interventions have been effective in reducing smoking [15-18] and have results comparable with those of other empirically supported treatments (ie, cognitive behavioral therapy) [18]. Most importantly, mindfulness is linked to underlying mechanisms associated with abstinence, such as decreasing negative affect [19-23], increasing positive affect [20,23,24], increasing self-efficacy [25-28], and lowering craving [29-32]. Nonetheless, studies that have examined mindfulness for smoking cessation have typically used the traditional format of mindfulness interventions (8 weekly group sessions lasting 2-2.5 hours). Although the results have been promising, this format is time- and resource-intensive and may discourage engagement, particularly among low SES populations. It is very likely that aspects of mindfulness, when delivered at key moments during the quit smoking process, can also be beneficial.

### Microrandomized Trials

This study uses a microrandomized trial (MRT) design to deliver mindfulness strategies (referred to as ecological momentary interventions [EMIs]) to participants on a smartphone at key moments during a quit attempt. Using MRTs is an innovative way to investigate whether certain intervention components, when delivered at certain times, impact hypothesized mechanisms and behavior [33]. We are specifically interested in the impact of these EMIs in relation to negative affect and lapse [4,6,34-37]. Thus, during a quit attempt, moments will be randomized to either receive a strategy or not, based on (1) times of low and high negative affect and (2) smoking status (lapse and no lapse). Negative affect and smoking status will be detected unobtrusively via wearable wireless sensors, and EMIs will be delivered via smartphones.

### Study Aims

This feasibility study will evaluate the provision of real-time, real-world mindfulness intervention strategies among a sample of smokers making a quit attempt. Outcomes are consistent with those evaluated in other feasibility studies [38,39]. Our feasibility outcomes will include participant retention, adherence, and score on the System Usability Scale. We will also measure acceptability outcomes that will include response to the Client Satisfaction Questionnaire and mindfulness strategies. As an exploratory outcome due to the small sample size, we hypothesize that providing mindfulness strategies in real time will be associated with lower negative affect, greater self-regulatory capacity, and a reduced likelihood of lapsing.

### Goal of the Paper

This paper will describe the protocol for Time2QuitMindfully, which is a study that will evaluate the feasibility of an MRT to deliver mindfulness strategies at key moments in the real world during a quit smoking attempt.

## Methods

### Recruitment

All recruitment and study procedures have been approved by Moffitt Cancer Center’s institutional review board. This study aims to recruit 24 participants who are interested in quitting smoking. To be eligible, participants must be aged 18 years or older; smoke an average of at least three cigarettes per day over the past year; have a carbon monoxide (CO) reading of at least six parts per million (ppm); are motivated to quit within the next 30 days; have a valid home address; have a functioning telephone number; and can speak, read, and write in English. Individuals will be ineligible if they have a history of contraindications for using the nicotine patch unless a doctor’s note is provided, endorse current psychosis, have a pacemaker or implanted device similar to a pacemaker, use smoking products other than cigarettes and e-cigarettes, are pregnant or trying to become pregnant or are breastfeeding, physically unable to wear the equipment and provide good readings of physiological measures, currently trying to quit smoking, involved in a quit smoking program, using tobacco cessation medications, have another household member enrolled in the study, or have no prior experience using a smartphone.

### In-Person Procedures

#### Recruitment, Orientation, and Study Visits

Participants will be recruited from the community via a variety of methods: community flyers, web-based advertisements, and prior study databases containing the contact information of participants who agreed to be contacted about future research opportunities. Interested individuals will be screened over the phone to assess their eligibility. If eligible, individuals will be given more details about what the study entails and will be invited to schedule an in-person orientation session, which will take place either in a group or individually. At orientation, the informed consent process to collect eligibility data will be conducted. Next, individuals’ CO will be measured to assess smoking status, a pregnancy test will be performed to rule out pregnancy, and the Mini International Neuropsychiatric Interview [40] will be conducted to rule out psychosis. If eligible, they will be shown a PowerPoint presentation to learn more about the study and to ask questions. After the PowerPoint presentation, participants who are interested in participating will be scheduled to attend the study visits.

The visit schedule is as follows: visit 1 is scheduled to occur 4 days before the quit day, visit 2 is on the quit day, visit 3 occurs 3 days after the quit day, and visit 4 occurs 7 days later. At 28 days after quit day, participants will return for a follow-up visit at visit 5. Figure 1 shows an overview of the timeline of the study sessions. Most sessions will last 1-3 hours, with visit 1 being the longest session at 3 hours.

**Figure 1 figure1:**
[figure not shown]
Study timeline. Ax: assessment; EMA: ecological momentary assessment; NRT: nicotine replacement therapy.

At the beginning of visit 1, participants will complete the informed consent process for study participation, which involves the experimenter explaining the purpose of the study, why they are being asked to participate, that participation is voluntary, what will happen during the study period, benefits, risks, and confidentiality. All study information presented at orientation will be revisited at visit 1, before having participants sign the informed consent document. After consent is complete, participants will be asked how many cigarettes they currently smoke per day to determine the correct dosage for nicotine replacement therapy (NRT) administration (details of patch administration described further below). CO, height, and weight will be measured, and participants will complete a battery of baseline questionnaires. Questionnaires measure constructs such as mindfulness, stress, anxiety, tobacco history, financial strain, and previous use of technology. The full list of questionnaires for each visit is presented in Table 1.

In the second portion of visit 1, participants will be trained in detail on how to use the study equipment. First, all pieces of equipment (2 wrist sensors, 1 chest box, 1 chest band, 2 types of electrodes, and 1 study phone) will be laid out on a table, and each piece of equipment and their purpose is to be explained in detail by the experimenter. The experimenter will then assemble the equipment on a mannequin one by one to demonstrate how equipment should be worn and will answer any questions along the way. Participants will be presented with their own set of equipment and asked to put it on, and the experimenter will leave the room. The experimenter will then return and check for correctness. After this is completed, there will be a discussion with the participants to ensure they will be wearing the sensors every day (at least 8-12 hours), and to set up a start and end time for each day on the phone.

The experimenter will then go through a participant packet that explains how to put on the equipment and navigate the study apps’ features, such as privacy mode (participants can choose if they do not want data collected for a period of time). The packet also details how to identify data quality, access the troubleshooting features, take off the equipment, end data collection if needed, and charge the equipment overnight. General information on how to use a smartphone and tackle common issues, such as poor data quality, will also be addressed. Before the session is over, the experimenter will ensure that all data quality collected on the phone is optimal and that the equipment is functioning as expected. Participants will also be provided phone numbers to contact if they experience any equipment issues. Equipment training will take approximately 1 hour to complete. At the end of the visit, participants will receive brief counseling and will be given instructions on wearing the patches for their quit day (visit 2). More details on the intervention are provided below.

During visits 2, 3, and 4, the following procedures will occur: assessment of cold or flu-like symptoms since the last visit (to account for if needed when analyzing physiological data), CO collection, administration of questionnaires, equipment check, presentation of technology boosters and provision of additional electrodes, brief counseling, and patch administration. Participants are to return their assigned equipment at visit 4, after 2 weeks of use. A follow-up visit will occur 28 days after quit day (visit 5), where tobacco use will be assessed, questionnaires completed, patches administered, and quit smoking resources provided.

**Table 1 table1:** Study measures overview.

Measure			Visit 1, baseline (−4)		Visit 2, quit day (0)		Visit 3, (+3)		Visit 4, end of Tx^a^ (+10)		Visit 5, follow-up (+28)
Demographics			X^b^		—^c^		—		—		—
**Agency and acculturation**											
	Self-Efficacy Scale-Smoking [41]	X		X		X		X		X	
	Financial Strain Measure [42]	X		—		—		—		—	
	Subjective Social Status [43]	X		—		—		X		X	
**Affect, stress, alcohol, and mental health**											
	Positive and Negative Affect Scale [44]	X		X		X		X		X	
	Perceived Stress Scale [45]	X		X		X		X		X	
	Alcohol Use Disorders Identification Test [46]	X		—		—		X		X	
	Patient Health Questionnaire-Alcohol [47]	X		—		—		X		X	
	Center for Epidemiologic Studies Depression Scale [48]	X		—		—		X		X	
	Generalized Anxiety Disorder-7 [49]	X		—		—		X		X	
	Distress Tolerance Scale [50]	X		—		—		X		X	
	Difficulties in Emotion Regulation Scale-Short Form [51]	X		—		—		X		X	
**Mindfulness and personal resources**											
	Shift and Persist [52]	X		—		—		X		X	
	Five Facet Mindfulness Questionnaire [53]	X		—		—		X		X	
	Mindful Attention Awareness Scale [54]	X		—		—		X		X	
	Mindfulness Self-efficacy [28]	X		—		—		—		X	
	Toronto Mindfulness Scale [55]	X		X		X		X		X	
**Smoking**											
	Wisconsin Smoking Withdrawal Scale [56]	X		X		X		X		X	
	Brief Wisconsin Inventory of Smoking Dependence Motives [57]	X		—		—		X		X	
**Smoking status and biochemical verification**											
	Tobacco history	X		—		—		—		X	
	CO^d^ reading	X		X		X		X		X	
	TLFB^e^	—		X		X		X		X	
	Tobacco Abstinence Questionnaire	—		X		X		X		X	
**Other**											
	Experience with technology survey	X		—		—		—		—	
	Experience with mindfulness survey	X		—		—		—		—	
	System Usability Scale [58]	—		—		—		X		—	
	Feasibility of technology survey	—		—		—		X		—	
	Mindfulness strategies feedback survey	—		—		—		X		X	
	Client Satisfaction Questionnaire [59]	—		—		—		X		—	

^a^TX: treatment.

^b^Procedure occurred at the indicated visit.

^c^Procedure did not occur at indicated visit.

^d^CO: carbon monoxide.

^e^TLFB: timeline follow back.

#### Check-Ins and Troubleshooting With Study Staff

During the 2 weeks of participants wearing the data collection equipment (visits 1-4), the study staff will monitor equipment use via a dashboard. Staff members will be able to see the quality of participant data (eg, wrist sensors, electrocardiography, and respiration) as well as whether participants have been receiving and completing surveys and strategies on the study phone. To troubleshoot and resolve issues, participants will be contacted if poor or no data appear in the system. Participants will be given phone numbers to contact if they experience issues during business hours and weekends.

#### Compensation and Incentives

Participants will be compensated at the end of each visit for completing questionnaires and to cover the costs of transportation, childcare, etc. At orientation, the participants will be compensated with US $10 for attending. At visits 1-3, participants earn US $30 in each session and US $50 at visits 4 and 5. Participants can also earn bonuses throughout the study by answering survey questions administered daily via the study phone. Participants will be compensated with US $1.25 for completing each phone survey if they have worn the on-body sensors at least 60% of the time since the last phone survey or US $0.50 for completing each phone survey if they have not worn the sensors at least 60% of the time. This pay schedule was developed to encourage continuous use of the equipment [60]. Depending on how often participants wear the on-body sensors and complete the surveys over the 14 days, they can earn US $0-$11.25 per day, for a total of US $0-$157.50 over the entire study, in bonuses.

### Equipment

At visit 1, participants will be given a set of equipment to wear for 2 weeks. The equipment suite is called AutoSense [61] and consists of a Samsung Galaxy S5, 2 wrist sensors that look and feel similar to watches or Fitbits, a chest box, and a chest band (Figure 2 shows an image of the equipment) [62,63]. The study phone will have the mCerebrum software [64] that restricts the participant to only accessing the study app when using the phone; this procedure is in place to reduce the use of the phone battery. When the participant turns on the phone, they will see a home page with the study’s contact information and app icon that will lead them directly to the app. The phones will upload data automatically to the Cerebral Cortex cloud [65] and include battery packs that make all-day use possible.

**Figure 2 figure2:**
[figure not shown]
Autosense equipment.

Participants will be given 2 wrist bands that are labeled with either an L or R on the straps, so that they can be placed on the appropriate wrist for data collection. The chest strap can be adjusted to accommodate a participant’s size, and participants will be instructed to wear the band around their chest right under the armpits, under their clothes. The strap has 2 ports where the chest box can be connected. The chest box is a small white box with 2 sets of wires clipped onto the chest band. One set of wires will connect to ports located on the chest band. The other set of wires will connect to the electrodes that are to be placed in the middle of the chest, right below the sternum, and on the left-hand side of the ribcage. Participants will be given 2 types of electrodes and instructed to wear what they are most comfortable with. Participants will also be provided a charging station and a draw string bag to transport their set of equipment and other materials to and from the laboratory.

#### Ecological Momentary Assessments/Surveys on Phone

Ecological momentary assessments (EMAs) will be delivered randomly within prespecified time blocks as well as after a subset of EMIs during the 2-week period. All methodologies for randomly allocating EMAs were preprogrammed using a random number generator function. Randomization also considers what has already been sent historically during that day and is based on certain conditions, as described below. Random EMAs are delivered within 3- to 4-hour blocks throughout the day. Thus, participants will receive no more than 1 survey per 4-hour block to limit the participant burden (up to 3 random EMAs per day). The system is also configured to deploy EMAs after EMIs (described below), 50% of the time. For an EMA to be delivered, certain conditions must be met: time since the last delivered EMI followed by EMA must be more than 15 min, data quality must be classified as good (ie, sensors are attached correctly to the user and the sensors are communicating correctly with the smartphone; red, yellow, and green indicators will be visible to participants so they can fix the equipment if needed. This allows for the sensor data collected in the vicinity of the moment of EMA to be available for analysis), and the participant cannot be driving or engaging in physical activity (to increase the likelihood of responding) [66].

When it is time to take a survey, participants will receive a notification on their phone. Participants will have the option of completing it, delaying it for 5 min, or canceling it altogether. EMAs take an average of 3-5 minutes to complete and assess the following broad areas: mindfulness, affect, motivation, urge to smoke, expectancies, self-efficacy, smoking behaviors, patch use, social setting, alcohol use, discrimination, stressors, and general emotional support. An item assessing whether participants have been using the mindfulness strategies, without the aid of their smartphone, will also be presented.

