### Intervention Components

#### EMIs

The use of technology in this study allows participants to receive interventions in real time via the study smartphone in their natural environment. The study app on the phone has been configured to deploy specific interventions triggered by smoking status or the level of negative affect. Data are continuously collected via the sensors. Here, we describe the content of the EMIs, followed by the delivery procedure.

Active strategies include prompts to engage in mindfulness-based strategies and read motivational messages throughout the day. The majority of messages will be mindfulness strategies (n=76), which fall into the following topic areas: breath (eg, Turn your attention to your breathing. Notice where you feel your breathing most in your body), thoughts (eg, Observe any thoughts you are having right now. Watch them go by, just as leaves float down a stream of water—they just come and go), sensations (eg, Shift your attention to what you see around you. Be aware of the colors, shapes, textures, and shadows for the next several moments), acceptance/nonjudging (eg, Try to let go of labeling things as good or bad. Be present with what is happening and suspend judgment), and craving (eg, Whenever you have a craving to smoke, think of the craving like a wave in the ocean—it will come and go over time). Examples of motivational messages (n=40) are: “Quitting smoking may be uncomfortable at times, but it will get easier! Your cravings will become less frequent and less intense the longer you go without smoking. Don’t give up!” Figure 3 provides screenshots of the example strategies shown to the participants.

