The day is separated into six 2-hour blocks for the delivery of EMIs. The decision point for randomization (ie, to send an active strategy or not) is based on smoking status and negative affect, both of which are being continuously monitored every minute while the equipment is being worn. For high negative affect, the decision to randomize is made as soon as a high negative affect event is detected within a 2-hour block and the participant is available. For lapse (ie, the detection of smoking), the decision to randomize is also made as soon as smoking is detected within the 2-hour block and the participant is available. Within a 2-hour block, this process is limited to one randomization occasion for high negative affect and one randomization occasion for lapse. For low negative affect, the decision point to randomize is randomly chosen at the start of the block, and if available when that time arrives, randomization occurs. If the participant is not available, another time is randomly chosen within that time block, and when that time arrives, assuming the participant is available, randomization occurs. This pattern is repeated until the end of the block. The process for randomization for no lapse is identical to the process of low negative affect, as previously described. Within a 2-hour block, randomization is limited to one occasion for low negative affect and one occasion for no lapse. In summary, up to 4 randomizations can occur within a 2-hour block (high negative affect, lapse, low negative affect, and no lapse). Moments will be randomized to receive a strategy or not in a 1:1 manner, and factors to ensure this 1:1 randomization will be included in the algorithm (ie, inclusion of historical data of what has already been triggered that day). Figure 4 shows the process of randomization based on the detection of high negative affect (low negative affect, lapse, and no lapse processes are not included in the figure for simplicity purposes, but their procedures mimic what is shown for high negative affect).

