**Figure 4 figure4:**
[figure not shown]
Randomization process based on the detection of high negative affect (low negative affect, lapse, and no lapse are not represented here for simplicity purposes). R: randomization.

When considering low/high negative affect and lapse/no-lapse occasions, participants can receive up to 2 active strategies within a block (ie, they receive a mindfulness strategy or motivational message). Thus, participants can receive up to 12 active strategies per day. Other conditions are also considered for the delivery of the strategies. These include time since last EMA being at least 15 min, time since last EMI being at least 30 min, good quality data detected via sensors, no driving, phone battery level at least 10%, and no engagement in physical activity. Given the above conditions for the delivery of EMIs, we do not anticipate individuals receiving more than 6 per day, and they may even receive fewer than 6. For instance, if someone does not lapse, then no strategies are sent for that purpose. AutoSense will not send messages when it detects driving, so no messages are sent during those times.

When active strategies are sent to participants, they will receive a notification on the phone, allowing them to know that a strategy is available. They will have the option of accepting it, delaying it for 5 min, or canceling it altogether. When participants agree, they will have the option of receiving a new strategy if they do not like the first one that appears on the phone. Participants will then let the app know whether they completed the strategy, and if they indicate *yes*, they will be asked to rate how much they liked the strategy on a scale of 1 to 5 stars. If they select 1 star, then this strategy will not be shown again to the participant.

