#### Analytic Plan

Descriptive statistics (eg, means and percentages) will be derived for feasibility and acceptability outcomes. Given that this is a feasibility study, sensor-driven analyses will be exploratory with the goal of providing preliminary results. The unit of analysis is the pre/postengagement data pairs comparing the average negative affect, self-regulatory capacity, and lapse counts within a prespecified time frame (eg, negative affect and self-regulatory capacity in the 30 minutes before and after randomization and lapse status in the time period between randomization of EMIs). These data will be analyzed using a generalized linear mixed model with proper adjustment for the within-subject correlation. The model can also include indicators for the category of mindfulness strategy. Each variable pair (negative affect, self-regulatory capacity, and smoking) will be analyzed separately in a pre/postengagement comparison to determine whether the mindfulness intervention creates any changes in these variables when compared with receiving no strategy at all. Examples of potential time-invariant covariates that will be included in the model are gender, age, education level, baseline trait mindfulness, and nicotine dependence. Time-varying covariates to be considered in the models include smoking status and use of the *on-demand* mindfulness content. Given that MRTs require unique considerations regarding data analysis (eg, participant availability and changes in the use of the intervention over time), we will incorporate the most recent recommendations in the literature when examining the data [69,70].

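### The strategy-versus-none contrast measures a bundle (mindfulness or motivational message, with a possible follow-up survey), yet the Analytic Plan attributes it to the mindfulness intervention

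*Protocol article*

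**What the plan says.** All references are to the protocol article.

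- **What is randomized.** EMIs section, after Figure 3: "Moments will be randomized to receive a strategy or not in a 1:1 manner". No other randomization of intervention content is described.
- **What an active moment contains.** EMIs section, after Figure 4: "participants can receive up to 2 active strategies within a block (ie, they receive a mindfulness strategy or motivational message". On the message pool, the EMIs section says "The majority of messages will be mindfulness strategies (n=76" and "Examples of motivational messages (n=40) are".
- **Surveys tied to strategies.** Ecological Momentary Assessments/Surveys on Phone: "The system is also configured to deploy EMAs after EMIs (described below), 50% of the time". The Microrandomized Trials section describes the design as one "to deliver mindfulness strategies (referred to as ecological momentary interventions [EMIs]) to participants on a smartphone", so an EMI is a delivered strategy. A survey takes 3-5 minutes and covers, among other things, mindfulness, affect, urge to smoke and stressors.
- **Payment.** Compensation and Incentives pays up to $1.25 per survey and says "they can earn US $0-$11.25 per day", or up to $157.50 over 14 days.
- **What the comparison is for.** Analytic Plan: "to determine whether the mindfulness intervention creates any changes in these variables when compared with receiving no strategy at all". Its example window for negative affect and self-regulatory capacity is 30 minutes either side of randomization. It allows optional indicators, but only for categories of mindfulness strategy.

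**The concern.** A randomized contrast estimates the effect of everything that differs between the two conditions. Two things besides mindfulness content appear to differ here. Some active moments carry a motivational message, and some are followed by a paid survey that asks about affect, urges and mindfulness itself and so could act as a prompt. The Analytic Plan nevertheless names mindfulness as the cause, and the optional indicators address neither component.

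At stake is what the feasibility data are taken to show. The abstract and the Discussion frame the result as preliminary evidence on mindfulness strategies, and the Discussion says the findings can inform how mindfulness acts on mechanisms. If the plan is followed as written, a difference produced by motivational messages or by being surveyed would be reported as a mindfulness effect and carried into the design of a larger trial.

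**Working it through.** **1. Reproduce the payment ceiling, to see which moments the surveys appear to follow.** Inputs: six 2-hour blocks, up to 4 randomizations and up to 2 active strategies per block (EMIs section); up to 3 random surveys a day and the 50% rule (survey section); $1.25 per survey and 14 days (Compensation and Incentives).

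- After active strategies only: 6 × 2 = 12 strategies; 0.5 × 12 + 3 = 9 surveys; 9 × $1.25 = $11.25 a day; × 14 = $157.50. Both stated figures reproduce exactly.
- After half of all randomizations: 6 × 4 = 24; 0.5 × 24 + 3 = 15 surveys; $18.75 a day and $262.50 in all. Does not reproduce.
- Using the anticipated 6 strategies a day at 50%: 0.5 × 6 + 3 = 6 surveys; $7.50. Does not reproduce.
- Six strategies, each followed by a survey: 6 + 3 = 9 surveys; $11.25. Reproduces, but contradicts the 50%.

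The reading that best fits the document's own figures is that the extra survey follows active strategies only. The ceiling counts surveys, however; it does not say which moments trigger them.

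**2. Message mix.** Pool: 76 + 40 = 116. Mindfulness 76/116 = 65.5%; motivational 40/116 = 34.5%. These are pool shares, not delivered shares.

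**3. What the pooled contrast estimates.** Let s be the mindfulness share of active moments, p the share followed by a survey, and dM, dQ and dE the effects of mindfulness content, motivational content and the survey. Assuming the effects add:

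contrast = s·dM + (1 − s)·dQ + p·dE

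Take s = 0.655 (messages drawn in proportion to the pool) and p = 0.5 (the ceiling). Mindfulness without a survey is then 0.655 × 0.5 = 0.328 of active moments. Other assumed values span 0.25 (s = 0.5, p = 0.5) to 0.80 (s = 0.8, p = 0).

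Illustration with invented effects:

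- dM = 0.3, dQ = dE = 0: 0.655 × 0.3 = 0.197.
- dM = 0, dQ = 0.3, dE = 0.2: 0.345 × 0.3 + 0.5 × 0.2 = 0.103 + 0.100 = 0.203.

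Nearly the same contrast arises with and without any mindfulness effect.

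**4. Timing of the survey.** The lag from strategy to survey is not stated. A survey completed wholly inside the example window fills 3/30 to 5/30, or 10-17%, of it. If the 15-minute spacing condition is read as a lag, then 15 + one 5-minute delay + 3 to 5 minutes ends at about 23 to 25 minutes, still inside the window. This is a reading of the text, not something it states.

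**5. Precision of component estimates.** Take n active and n no-strategy moments, independent and with equal variance. Using a fraction f of the active moments, the standard error relative to the pooled contrast is sqrt((1/f + 1)/2).

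- Strategy without assigned survey, f = 0.5: sqrt((2 + 1)/2) = 1.22.
- Mindfulness without survey, f = 0.328: sqrt((3.05 + 1)/2) = 1.42.

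**The case against.** The strongest reply is that the bundle is openly described, that its comparison with nothing is a sound randomized contrast, and that the document makes no efficacy claim. The sensor analyses are labelled exploratory, the Discussion says the small sample limits conclusions, and efficacy is left to a larger trial. This stands and limits the seriousness of the point. It does not repair the attribution. The limitations that the Discussion lists include counseling and nicotine replacement, which every participant receives, but neither component that differs between the randomized conditions.

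A second reply is that component splits and survey covariates belong in an analysis plan that is not shown. That holds for modelling detail. It does not hold for the purpose the protocol itself gives the contrast.

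Three stronger readings are tempting, and the documents do not support them:

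- *That no-strategy moments are free of surveys.* No sentence says so. The inference rests on the EMI definition and the payment ceiling, and the term EMI is used loosely elsewhere. Random surveys can fall near either kind of moment, so exposure is probably unequal rather than absent on one side.
- *That half of strategy moments carry a survey inside the outcome window.* The 50% is a ceiling: delivery also needs good data, no driving and no physical activity, and a survey can be delayed or cancelled. The lag is unstated and the window is only an example.
- *That mindfulness without a survey should become the lead contrast.* Message type is not described as randomized. Content depends on quit phase, lapse status and earlier one-star ratings, so that comparison could confound message type with the participant's state.

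**Conclusion.** The point holds as a fault of attribution. The motivational limb rests on explicit text: an active strategy may be either kind of message, and 34% of the pool is motivational. The survey limb is well supported but inferred; where the survey falls within the outcome window, it is a second difference between conditions.

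The randomized contrast is not biased for the bundle and nothing here invalidates it. What does not follow is a conclusion about mindfulness content. A reader might also infer that the mindfulness effect is diluted by about a third. That would need messages drawn in proportion to the pool and motivational messages that do nothing, and the document states neither.

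The point is worth correcting, because it changes what may be concluded at little cost. Its weight is moderate, because the analysis is exploratory within a feasibility study planned for 24 participants.

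**What to change.** 1. Keep the randomized pooled contrast as the lead. Label and interpret it as any active strategy (mindfulness or motivational, with possible follow-up survey) versus none, and carry that wording into the conclusions.
2. State whether moments randomized to no strategy can trigger a follow-up survey, and the lag from strategy to survey.
3. Add two secondary exploratory analyses:
   - (a) An indicator for message type, mindfulness versus motivational, adjusted for quit phase, lapse status and trigger type because type is not described as randomized. Use the first-assigned message, since participants may ask for another.
   - (b) Strategy without an assigned survey versus none, using the random 50% draw rather than surveys delivered or completed, since those depend on sensor quality, activity and the participant's choice.

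The relabelling costs nothing. The secondary analyses cost coding and precision: standard errors about 1.22 times the pooled one for (b), and about 1.42 times if narrowed to mindfulness without survey, under the assumptions shown. They also depend on the draw and the first-assigned message having been recorded. The staff dashboard shows receipt and completion of surveys and strategies, but the protocol does not say that these two items were kept. If they were not, the relabelling alone still corrects the interpretation.
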